## Our studies in 1998/9 showed that artesunate, in combination with SP, reduced both the mean density of gametocytes in positive subjects, and the prevalence of gametocytes in the treated population (7) compared to SP alone. Nevertheless, a gametocyte prevalence of 5-10% was observed at day 7 in the combination group, and these gametocytes were capable of infecting mosquitoes in membrane-feeding experiments (7). Therefore, there may still be considerable transmission after treatment with artesunate combined with SP.

In 2000, we compared treatment with the combination chloroquine plus artesunate (3 days) with chloroquine alone. We have not completed analysis of this trial yet, as a duplicate slide-read is currently ongoing, but the following summary of our preliminary findings can be made:

- parasitological treatment failures with chloroquine alone were very common, the cumulative rate at day 28 approaching 60% (although this is a crude figure which includes re-infections)
- parasitological treatment failures with chloroquine plus artesunate were also unacceptably high, with a cumulative rate at day 28 of 39%, although on average these occurred much later in follow-up that failures with chloroquine alone.
- Clinical failures mirrored this pattern, with cumulative failure rates by day 28 of 12% and 8% respectively. The addition of artesunate to chloroquine treatment significantly reduced the probability of a child returning with clinical malaria within 14 days of treatment, but this benefit was not observed in the latter half of follow-up.
- Gametocyte carriage was significantly reduced in the combination group up to day 14, but day 28 gametocyte carriage rates were high in both groups: 34% for chloroquine and 21% for chloroquine +artesunate.
- Children identified as gametocyte carriers on day 7, but who were gametocyte-negative on admission, were tested for infectiousness to *Anopheles*. Some gametocyte-carriers from both groups were infectious (12/26 for the chloroquine group; 4/17 for the combination group), although gametocytes from children receiving chloroquine plus artesunate were less infective.

We conclude from this preliminary analysis that whereas addition of artesunate to chloroquine does reduce transmission immediately post-treatment, the emergence of asexual and sexual parasites in the 3rd and 4th weeks greatly reduces this benefit over the longer term.

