In our 1998, 1999 and 2000 trials based at the Farafenni Health Centre we recruited 600 children over 15 weeks, 500 children over 10 weeks, and 536 children over 9 weeks respectively. These rates of subject recruitment, combined with gametocyte prevalence data from each year will be fed into the study design to ensure sufficient mosquito feeds across the treatment groups.

We will analyse the results of the trial for all the relevant clinical, parasitological and entomological parameters available to us. In addition, we have used two summary statistics (the probability of post-treatment infectiousness, and the infectious proportion of subjects) that incorporate gametocyte prevalence, density and infectivity to mosquitoes (7). These data will then be related to the estimated proportion of treated infections in rural areas of The Gambia to derive an estimate of the contribution that children treated with each regimen would make to transmission.

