**B3 Details of study design and investigations**

1. **What type of study design is proposed (eg case control, prospective cohort, randomised controlled trial, descriptive etc)**

Randomised Control Trial

1. **What is the proposed size of the study (this may relate to patients, cases, controls, survey subjects, laboratory samples etc, as appropriate).**

The aim is to recruit approximately 500 patients, to have a minimum of 25 individuals per group who provide a blood sample for membrane feeding.

1. **Please describe the statistical considerations and sample size calculations involved in determining the size of the study.** (If you do not have access to statistical advice, please consult the MRC Laboratories Statistics Department.)

Approximately 500 patients will be treated. In our previous studies the observed gametocyte carriage rate 7 days after treatment with SP was >70% (excluding those who had gametocytes on day 0), and 40% after treatment with CQ. We therefore expect that the rate after SP + CQ will be at least 28% (ie 40% x 70%). Therefore, to ensure that at least 30 mosquito feeds are performed in each treatment group, we will aim to enrol **a)** 200 subjects in the CQ + SP group, **b)** 50, 60 and 70 subjects in the 3 groups receiving SP and being screened for gametocytes on days 7, 10 and 14 respectively, and **c)** 130 subjects in the CQ group. All CQ- and CQ + SP-treated children will be screened for gametocytes on day 7 only. This will provide sufficient power at the 90% confidence level to detect a 10-fold difference in infectiousness at day 7 between gametocyte-positive children treated with SP alone, and those treated with SP + CQ.

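### The enrolment numbers do not ensure 30 mosquito feeds per group: no carrier-to-feed loss is allowed for, the SP day-7 group has almost no margin, and the same section also gives a minimum of 25

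*Protocol*

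**What the plan says.** All of the sizing is in Protocol section B3. The answer on study size asks for about 500 patients, "to have a minimum of 25 individuals per group who provide a blood sample for membrane feeding". The next answer, on statistical considerations, sets the enrolments "to ensure that at least 30 mosquito feeds are performed in each treatment group".

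The rates used are day-7 gametocyte carriage in earlier studies. The carriage rate after "treatment with SP was >70% (excluding those who had gametocytes on day 0"), and it was "40% after treatment with CQ". From these the protocol expects that "the rate after SP + CQ will be at least 28% (ie 40% x 70"%).

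The enrolments are "200 subjects in the CQ + SP group", 130 in the CQ group, and 50, 60 and 70 in the SP groups screened on days 7, 10 and 14. The power statement covers one contrast: infectiousness at day 7 of gametocyte-positive children, SP alone against SP + CQ.

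Under Clinical trial and transmission experiments, blood for feeding is taken only if the child comes for screening, the slide shows gametocytes and permission is given. The same part gives 2000 recruitment within "500 children over 10 weeks, and 536 children over 9 weeks respectively". The Background reports that some gametocyte carriers tested in 2000 "were infectious (12/26 for the chloroquine group; 4/17 for the combination group").

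**The concern.** The calculation goes straight from carriage to enrolment and treats a carrier as a feed. No allowance is stated for missed screening visits, refused venepuncture or failed feeds. The SP rate comes from children without gametocytes on day 0, but it appears to be applied to all 50 enrolled, and the entry criteria do not exclude day-0 carriers.

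Infectivity to mosquitoes is one of the trial's outcome measures, and the powered comparison is made among children who are fed. The number of feeds, not the number enrolled, is therefore the effective sample size. If SP day 7 falls short, the one contrast with a power claim is weakened on its smaller side, and extra children in CQ+SP only partly make up for that. The reader also cannot tell whether the design promises 25 or 30.

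**Working it through.** **Inputs (Protocol B3).** Carriage: SP 70% (stated as more than 70%), CQ 40%, CQ+SP 28%. Enrolment: SP 50/60/70, CQ 130, CQ+SP 200, total 510. Target: 30, or 25. No carriage is given for SP on days 10 and 14; 70% is assumed there.

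**The plan's own figures.** 0.40 × 0.70 = 0.28 reproduces the 28%, and 510 fits about 500. The enrolments are not simply 30 / carriage, which gives 43 (SP), 75 (CQ) and 108 (CQ+SP). Each day-7 group has some slack, but the slack is unequal and unexplained.

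**Expected carriers and the fed fraction needed.** Carriers = n × carriage; fraction needed = target / carriers.

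| Group | n | Carriers | Needed for 30 | Needed for 25 |
|---|---|---|---|---|
| SP day 7 | 50 | 35 | 86% | 71% |
| SP day 10 (assumed 70%) | 60 | 42 | 71% | 60% |
| SP day 14 (assumed 70%) | 70 | 49 | 61% | 51% |
| CQ | 130 | 52 | 58% | 48% |
| CQ+SP | 200 | 56 | 54% | 45% |

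**Chance of at least 30 feeds.** Feeds ~ Binomial(n, carriage × f), where f is the fraction of carriers fed (assumed values).

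| f | SP day 7: expected feeds | SP day 7 | SP day 10 | CQ | CQ+SP |
|---|---|---|---|---|---|
| 100% | 35.0 | 95% | >99% | >99% | >99% |
| 90% | 31.5 | 72% | 99% | >99% | >99% |
| 80% | 28.0 | 34% | 86% | 99% | >99% |
| 70% | 24.5 | 8% | 49% | 91% | 96% |
| 60% | 21.0 | <1% | 13% | 63% | 78% |

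**Day-0 carriers.** If 10% or 20% of the 50 carry gametocytes at entry (assumed) and are not fed, 45 × 0.70 = 31.5 or 40 × 0.70 = 28 feeds are expected with no other loss. The chance of reaching 30 is then 75% or 31%.

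**The 2000 trial.** 26 + 17 = 43 children were tested for infectiousness out of 536, or 8.0%. The arm sizes are not given, so the CQ arm's share s is varied. Fed fraction = 26 / (536 × s × 0.40).

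| s | CQ carriers in 2000 | Fed fraction | SP day 7 feeds | CQ feeds | CQ+SP feeds |
|---|---|---|---|---|---|
| 25% | 53.6 | 49% | 17 | 25 | 27 |
| 50% | 107.2 | 24% | 8 | 13 | 14 |
| 67% | 143.6 | 18% | 6 | 9 | 10 |

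A fed fraction of 86% would imply a 2000 CQ arm of about 26 / (0.857 × 0.40) = 76 children.

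**What 510 children can support.** For 30 expected feeds in all five groups the total is 30 × (3/0.70 + 1/0.40 + 1/0.28) / f = 310.7 / f. Setting this equal to 510 gives f = 61%. For 25 feeds the total is 258.9 / f, so f = 51%.

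**The case against.** The strongest reply is that the plan meets its target on its own inputs. Thirty-five expected carriers exceed 30, and if all are fed the chance of 30 feeds is 95%. Carriage is stated as above 70%; at an assumed 80% the chance is 98% with 90% fed and 77% with 80% fed. This stands. A reader might infer that the enrolments cannot deliver 30 feeds, and the document does not support that. It supports only that they do not ensure it.

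A reader might also take the 2000 counts as proof of a low yield. They are not proof. Arm sizes and the number of eligible carriers left unfed are not given. Feeding in 2000 was limited to children without gametocytes on admission, and the present methods do not repeat that limit. If day-0 carriers may now be fed, the day-0 loss above need not occur. Setting 8% of recruits against the 150 of 510 (29%) needed here is not like for like either, since one 2000 arm received artesunate, which lowered carriage.

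Nor does a shortfall by itself defeat the power claim. With Fisher's exact test at a two-sided 5% level, 46% infectious (12/26, borrowed from the 2000 CQ group) against one tenth of that gives 91% power with 17 and 27 feeds and about 62% with 8 and 14. At an assumed 30% base, 17 and 27 feeds give 64%. The effect depends on a base rate that the protocol does not state for SP.

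Finally, the protocol says that recruitment rates and gametocyte prevalence will inform the design, and recruitment could run beyond 500. That is an intention. It brings in no fed fraction and does not change the enrolments in B3.

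**Conclusion.** The point holds in limited form. The statement that the enrolments ensure at least 30 feeds in every group is unsupported, and it conflicts with the minimum of 25 in the same section. The conflict needs no assumption.

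The weakness is concentrated in SP day 7, which needs 86% of carriers fed (71% for the lower minimum). At 70% carriage its chance of 30 feeds drops from 95% to 34% once a fifth of carriers are not fed. CQ and CQ+SP tolerate losing over 40% of carriers. SP day 10 is the next weakest, if 70% carriage persists to that day.

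Calling 28% a lower bound is also wrong: it is the value expected if the two drugs act independently on carriage.

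The size of any real shortfall is unknown because the fed fraction is not stated. The 2000 range of about 17 to 6 feeds in SP day 7 is a warning that rests on assumed arm shares of 25% to 67%.

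**What to change.** Before the randomisation list is made:

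- Keep one minimum, 25 or 30, and use it throughout B3.
- Take the fed fraction of carriers and the share of day-0 carriers from the 1998–2000 records. State both, and say whether day-0 carriers may be fed.
- Size all five groups, including SP days 10 and 14, as target / (carriage × fed fraction), with a further allowance if day-0 carriers are not fed. State the carriage assumed for days 10 and 14.
- Stay within about 510 by moving places to SP day 7 from groups with more margin. Do not rebalance the three day-7 groups alone, because that leaves SP day 10 at 60, with a 49% chance of 30 feeds at 70% fed. Take places from CQ+SP cautiously, since its 28% may prove too high.
- Describe 28% as an expectation under independence.
- If the recorded fed fraction is below about 61% (for 30) or 51% (for 25), 510 children cannot give every group the target even in expectation. In that case replace the assurance with the feeds expected per group and restate the power statement for those numbers.

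The cost is a check of existing records, some rewording and a changed allocation ratio, with no extra children. The larger groups lose a little margin, and the stated figure may be less favourable.

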**For studies involving human subjects:**

1. **How and where will the study subjects (cases, controls, etc) be selected? Has it been confirmed that they are not already involved in other studies?**

Subjects will be enrolled at Farafenni AFPRC Hospital/MCH clinic from among children presenting with uncomplicated falciparum malaria. Recruits will be randomised among the treatment groups.

1. **What inclusion/exclusion criteria will be applied?**

##### Children aged 1-10 years and the informed consent from a parent or guardian.

##### Inclusion Criteria

Fever or history of fever and a parasitaemia > 500/ul of *P.falciparum*

Informed consent from a parent or guardian.

Aged 1-10 years.

##### Exclusion Criteria

Signs or symptoms of severe malaria including severe anaemia (PCV <15% or Hb<5g/dL), or hyperparasitaemia (>500 parasites per hpf).

Vomiting or unable to take drugs orally.

A history of anti-malarial treatment in the past two weeks.

Evidence of any other chronic or acute illness.

1. **How will informed consent be obtained?**

Informed consent will be obtained from a parent or guardian at the time of enrolment into the study. The aims and methods, including details of blood samples needed, will be explained in a language they understand. The recruiting field worker/nurse will sign that consent was given. The right of all individuals not to participate or to withdraw their consent will be respected and the children will then receive standard treatment. Parents may withdraw their consent at any point in the trial and the child’s treatment will not be affected.

1. **What samples, if any, will be taken and what investigations will be conducted?**

- Finger-prick blood samples on days 0, 7, 14 and 28 to provide thick films for parasite detection and filter paper blood spots for molecular typing.
- Microtainer samples on day 0 for PCV, genotyping and RT-PCR
- 2-3ml blood by venepuncture on day 7 OR 10 OR 14 from consenting gametocyte-positive patients for membrane feeding of mosquitoes.
- Alcohol-fixed oocysts from mosquito guts for genotyping

1. **Will treatment be given? YES**

**If yes:**

**Nature of treatment(s)**

For drugs: dosage and duration of treatment

- A single dose of sulphadoxine /pyrimethamine (Fansidar®): for children  10kg, 0.5 tablet of SP (12.5mg and 250mg respectively), with an additional quarter tablet for each additional 5kg.
- Chloroquine at a total dose of 25mg/kg over 3 days with a single dose of sulphadoxine /pyrimethamine (Fansidar®) as above.
- Chloroquine at a total dose of 25mg/kg over 3 days.
- Each child will also be given a stat. dose of paracetamol (10 mg/kg) at enrolment.

Children will be observed for one hour for vomiting. Any child who vomits the study medication within one hour will receive a second dose. Children who vomit a second time will be dropped from the trial and treated with sub-cutaneous chloroquine.

Person(s) responsible for administering treatment

- Farafenni malaria epidemiologist and other MRC clinicians

1. **For questionnaires/interviews, who will be conducting these?**

- Field assistants and nurses

1. **Who will be primarily responsible for the statistical design and analysis?**

- The principle investigator in collaboration with LSHTM and MRC statisticians

1. **Who will be primarily responsible for data management?**

- The Farafenni data manager in collaboration with the principle investigator

**C Ethical issues**

**Please highlight any potential ethical issues and how you propose to deal with these. What outcomes and benefits will derive from the study? How will the results of the study contribute to the health of the people of the Gambia?**

This section, together with B3 is particularly important to the Ethical Committee and should be comprehensive. Please continue on a separate sheet if necessary.

This is a continuation of studies designed to establish the drug or drugs most appropriate for use in interrupting transmission of malaria to mosquitoes and the benefits gained by use of associating artemisinins with other anti-malarials. The primary benefit to the participants is that, as well as receiving free treatment, after treatment at the clinic they will be monitored by field assistants visiting their homes. In addition, the patients have access to study clinicians at the daily recruiting clinic run by the research team in the old Farafenni Health Centre, or at MRC Farafenni Field Station should the need arise.

The benefit of selecting a drug(s) that prevent transmission comes with its use for mass treatment of a population prior to the transmission season. The expectation is that this would significantly reduce the source of malaria infection in the subsequent malaria season, with a consequent reduction in malaria morbidity and mortality.

Collection of blood samples will be done only after informed consent has been obtained.

Any child in the study in need of additional medical attention will be provided with the appropriate treatment or referred.
